## Abstract

**Introduction:**

Intravenous thrombolysis (IVT) and mechanical thrombectomy (MT) are well-established, evidence-based, time-critical therapies that reduce morbidity and mortality in acute ischemic stroke (AIS) patients. The exclusion of intracerebral hemorrhage (ICH) is mandatory and has been performed by cerebral imaging to date. Mobile stroke units (MSUs) have been shown to improve functional outcomes by bringing cerebral imaging and IVT directly to the patient, but they have limited coverage. Blood biomarkers clearly distinguishing between AIS, ICH, and stroke mimics (SM) could provide an alternative to cerebral imaging if concentration changes are detectable in the hyperacute phase after stroke with high diagnostic accuracy. In this study, we will take blood samples in a prehospital setting to evaluate potential biomarkers. The study was registered in the German Clinical Trials Register (https://drks.de/search/de) with the identifier DRKS00023063.

**Methods and analysis:**

We plan a prospective, observational study involving 300 patients with suspected stroke and symptom onset of ≤4.5 h before the collection of biomarkers. Study participants will be recruited from three sites in Berlin, Germany during MSU deployments. The focus of the study is the collection of blood samples from participants at the prehospital scene and from participants with AIS or ICH at a second-time point. All samples will be analyzed using targeted and untargeted analytical approaches. Study-related information about participants, including medical information and discharge diagnoses from the subsequent treating hospital, will be collected and documented in an electronic case report form (eCRF).

**Discussion:**

This study will evaluate whether a single blood biomarker or a combination of biomarkers can distinguish patients with AIS and ICH from patients with stroke and SM in the early phase after symptom onset in the prehospital setting. In addition, the kinetics of blood biomarkers in AIS and ICH patients will be investigated. Our goal is to evaluate new ways to reliably diagnose stroke in the prehospital setting and thus accelerate the application of evidence-based therapies to stroke patients.

## Introduction

Stroke is a major cause of mortality and disability worldwide (1). Cerebral imaging and clinical examination play a crucial role, and blood biomarkers may be useful in diagnosing and evaluating treatment options in stroke patients (2–4). Intravenous thrombolysis (IVT) and mechanical thrombectomy (MT) alone or in combination are established evidence-based revascularization treatments for acute ischemic stroke (AIS) patients (5, 6). However, the effectiveness of these therapies is highly time dependent (7), and the exclusion of certain contraindications before IVT is mandatory (8, 9). To date, intracerebral hemorrhage (ICH), one of the most important contraindications, is only reliably detectable by cerebral imaging, either with computed tomography (CT) or magnetic resonance imaging (MRI), which is thus mandatory before the initiation of IVT (10).

Mobile stroke units (MSUs)—ambulances with a CT scanner and a point-of-care (POC) laboratory on board—significantly reduce the alarm-to-treatment time (ATT) compared to regular care and increase the number of patients treated within 60 min after the onset of symptoms (11–14), two large studies (Berlin_PRehospital Or Usual Delivery of Acute Stroke Care (B_PROUD) and BEnefits of Stroke Treatment Delivered Using a Mobile Stroke Unit [BEST-MSU]) independently demonstrated that treatment on board an MSU led to a significant reduction in disability at 90 days (15, 16). Furthermore, in cases of large vessel occlusion (LVO), patients can be selectively transported to the next appropriate hospital offering mechanical thrombectomy.

The number of operational MSUs is increasing around the globe (Map of active MSUs: https://www.prestomsu.org/); however, maintenance and operational costs make them particularly suitable for use in urban areas (17, 18). Therefore, there is a substantial unmet need to explore new ways of diagnosing AIS, ICH, or diseases that mimic stroke [so-called stroke mimics (SMs)] without cerebral imaging, thereby reducing treatment times even outside the range of action of MSUs in the prehospital setting.

Identification of potential blood-based biomarkers may be a first step for the subsequent use of POC diagnostics in regular ambulances to distinguish AIS from ICH and SMs, initiate IVT in the prehospital setting, and improve patient allocation to specialized centers (19). In recent years, several blood-based biomarkers have shown promise for differentiating between AIS and ICH. These biomarkers include RBP-4, NT-proBNP, GFAP, FXII, plasminogen, and prolactin (20–22). Additionally, biomarkers such as S100B, MMP-9, and CRP (23) have been evaluated for their ability to distinguish between stroke and other acute neurological conditions in the early in-hospital phase (24–27). However, to date, no single blood biomarker or panel of biomarkers has been identified to replace cerebral imaging (28). Moreover, to the best of our knowledge, there are almost no studies on blood-based biomarkers during the very early prehospital phase or analyzing the kinetics shortly after the onset of symptoms (29). However, one study showed promising sensitivity and specificity regarding the kinetics of prehospital measured GFAP in differentiating between AIS and ICH (30).

Blood biomarkers must not only confirm the clinical diagnosis of AIS and rule out ICH with a high degree of certainty but also detect AIS and ICH very early after the onset of symptoms to start causal therapies as soon as possible. Most studies have investigated blood biomarkers only in the later in-hospital phase. Therefore, in this study, we plan a multicenter prospective observational study by drawing blood from patients who are treated in the prehospital field by an MSU neurologist and want to identify biomarkers suitable for the differentiation between AIS, ICH, and SMs.

## Methods and analysis

The manuscript was written according to the SPIRIT 2013 guidelines for protocols and clinical trials (31).

### Study title

The name of the study, ProGrEss-Bio, is the translation of the German title “**Pro**spektive **G**ewinnung von Blutplasma-P**r**oben zur **E**rfa**ss**ung geeigneter **Bio**marker für die prähospitale Schlaganfallforschung.”

### Hypotheses

#### Primary hypothesis

One or a group of different blood biomarkers enables the differentiation between AIS and ICH in patients with acute stroke with sufficient sensitivity, specificity, and predictive values.

#### Secondary hypothesis

One or a group of different blood biomarkers enables the differentiation between acute stroke and SM in patients with suspected stroke with sufficient sensitivity, specificity, and predictive values. The kinetics of biomarkers in the early phase of a stroke may improve discriminatory power.

### Study design

ProGrEss-Bio (“prospective collection of blood plasma samples to identify potential biomarkers for the prehospital stroke diagnosis”) is a multicenter, prospective observational study that aims to investigate patients with suspected stroke within 4.5 h of the onset of symptoms. The study's primary objective is to identify blood-based biomarkers that can help in identifying stroke subtypes and differentiating between stroke and other acute neurological conditions imitating stroke, i.e. SMs. Details for the timeline can be found in Figure 1. The study is being conducted at three MSU study platforms (also known as Stroke Emergency Mobiles [STEMO]) of the Berlin Fire Department. Patients suspected of possibly having an acute stroke or SM based on the initial assessment of the MSU neurologist are recruited during routine prehospital care by the MSU neurologist. Details can be found in Figure 2.

**Figure 1 F1:**
[figure not shown]
Timeline. The timeline for the study from 2020 to 2023 is shown. The parts of the planning, administrative, and recruitment phases are depicted in the blue and green boxes. The analysis and publication phases are found in the red and yellow box. At the bottom of the graphic, the months and years are shown.

**Figure 2 F2:**
[figure not shown]
Conduction of the study. Procedure for including patients in the study is shown in chronological order from left to right. Boxes in red describe procedures during routine emergency treatment, and boxes in blue describe study-specific procedures. Blood samples will only be analyzed in cases where the patient or legal representative gives written informed consent. The blood sample is temporarily stored in the fire or rescue station and later in a biobank.

In contrast to many other studies, we plan to use a broad spectrum of potential biomarkers using a so-called “multi-omics” approach [proteins (proteomics), genes (genomics), ribonucleic acid (RNA [transcriptomics]), and metabolites (metabolomics)]. A second study-related blood sample will be collected from AIS and ICH patients 20 to 60 min after the collection of the first sample, usually done upon the patient's arrival at the hospital, the study allows for the examination of concentration changes and kinetics in the early phase. We plan to include 300 patients in this study. The study will be initially implemented at one MSU (STEMO 3600) and then rolled out to the other two MSUs. Universal trial number (UTN): U1111–1258-2477.

### Study population

#### Inclusion criteria

Participants are eligible for the study if they meet the following inclusion criteria:

Age ≥ 18 years.Suspected or possible stroke or SM based on the initial assessment of the treating MSU neurologist.Symptom onset of ≤4.5 h before the collection of biomarkers.Written informed consent will be obtained from the participant or their legal representative. Informed consent can be given up to 12 weeks after the collection of the biomarkers, but before further analyses, either by the patient or their legal representative.

#### Exclusion criteria

Participants who meet any of the following criteria are excluded from study entry:

Drawing blood is not possible, either for technical or medical reasons.Withdrawal of written consent for study participation by a participant or their legal representative. No informed consent is provided up to 12 weeks after drawing blood because, by then, blood samples will be destroyed.

The symptom onset refers to the information the MSU neurologist has at the scene, as it best reflects the real situation in the case of a possible IVT decision.

In cases of severe medical events in the days or weeks before drawing blood, e.g., myocardial infarction, the study physician can elaborate on these events in detail in an open field of the electronic case report form (eCRF). These events possibly affect the measurement of the blood biomarkers and are, therefore, usually recorded. Further pre-existing conditions, such as arterial hypertension, are mandatory fields in the eCRF.

### Outcomes

The main objective of this study is to discover blood-based biomarkers suitable for acute stroke therapies without cerebral imaging and thus potentially improve prehospital diagnosis. These biomarkers need to reliably detect strokes and distinguish between AIS and ICH. In addition, they should be rapidly measurable and readily available in as many regular ambulances as possible worldwide. Concentration changes of potential blood biomarkers must be reliably detectable very early after symptom onset in POC devices to start IVT as early as possible in the prehospital setting. In many studies, blood is drawn in the later phase of AIS; therefore, early concentration changes of these biomarkers are unknown. Additionally, we do not plan to only collect blood samples very early but plan to use novel proteomics, transcriptomics, and metabolomics approaches and thus investigate many biomarkers simultaneously. In some patients, statements about the kinetics will be possible since two blood samples at different time points are collected.

#### Primary and secondary targets

As this is an explorative study (discovery phase), the primary target is to identify a single blood-based biomarker, or a panel of biomarkers, with strong differentiation between the AIS and the ICH groups, i.e., to identify candidates for a prediction model that will then be tested and refined in a subsequent study.

The same is true for the secondary target, namely, to identify a single blood-based biomarker or, again, a group of markers with great differences between stroke and SM patients.

To this end, the absolute values of blood biomarkers and their kinetics in AIS and ICH patients will be determined. We expect a change in the concentration of biomarkers over time in the acute phase after AIS and ICH patients due to vascular injury and subsequent neuronal cell injury, whereas we expect no such changes in SM patients.

### Biomarkers

Out of the proteomics and metabolomics data, we plan to identify targets for the differentiation between AIS and ICH and between stroke and SM. Furthermore, we will measure single blood biomarkers previously tested and considered promising candidates for the differentiation between AIS, ICH, and SM. Therefore, we will measure apo CIII, copeptin, D-Dimer, endostatin, EGFR, eotaxin, FXII, GFAP, HSC-70, MMP inhibitor-4, MMP-9, prolactin, NT-proBNP, plasminogen, RBP-4, S100A12, S100-B, and UCHL-1 (20–23, 32–35).

### Collection and processing of data and samples

#### Blood sampling and processing

The first study-related blood sample will be taken after all steps of the necessary emergency treatment are completed. A second study-related blood sample in AIS or ICH will be drawn between 20 and 60 min subsequently, if possible, i.e., the patient will not be transported by regular ambulance alone or for other reasons, e.g., life-saving therapies are required, making the collection of a second blood sample impossible.

All tubes for each study participant will be individually pre-labeled, pre-coded, and packed with a unique identifier (ID). Identification of the study participants will only be possible with this unique ID. The following steps are shown in detail in Figure 3. Two ethylenediaminetetraacetic acid (EDTA) tubes (6 and 3 ml), one heparin tube (5 ml), one serum tube (5 ml) (VACUETTE^®^, blood drawing tubes, from Greiner Bio-One, Austria, Kremsmünster), a Tempus™-tube (3 ml) [TEMPUS™, blood ribonucleic acid (RNA) tube, Applied Biosystems™ by Thermo Fisher Inc., United States, Waltham, MA], and a small amount of blood in a full blood tube for international normalized ratio measurement and dry blood cards will be used for blood sampling in study participants. The serum tube will be collected first, and the Tempus™-tube will be the last.

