#### Tertiary analysis

Determination of the kinetics of blood biomarkers within the acute phase of a stroke (≤4.5 h after symptom onset) by drawing blood directly after MSU arrival at the scene and 20–60 min later to detect and observe early changes in the concentrations of blood biomarkers.

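### The article gives two incompatible times for the first study sample; if the later one governs, thrombolysis given to AIS but not ICH patients can confound the primary comparison

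*Protocol article*

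**What the plan says.** Two sections of the Protocol article time the same first draw.

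- Blood sampling and processing: "The first study-related blood sample will be taken after all steps of the necessary emergency treatment are completed".
- Tertiary analysis: the kinetics are to be determined "by drawing blood directly after MSU arrival at the scene", with a second draw 20–60 min later. The Discussion likewise presents sampling at the earliest opportunity as a strength of the study.

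Other sections bear on why the order matters. The Abstract describes MSUs as "bringing cerebral imaging and IVT directly to the patient". The Introduction says that IVT and mechanical thrombectomy "are established evidence-based revascularization treatments for acute ischemic stroke (AIS) patients", and that "intracerebral hemorrhage (ICH), one of the most important contraindications, is only reliably detectable by cerebral imaging". The Outcomes section gives the aim: to "discover blood-based biomarkers suitable for acute stroke therapies without cerebral imaging", so that IVT can start early. The Biomarkers section names the targeted candidates, among them "apo CIII, copeptin, D-Dimer, endostatin, EGFR, eotaxin, FXII, GFAP, HSC-70, MMP inhibitor-4, MMP-9, prolactin, NT-proBNP, plasminogen". Under Statistical analysis, each predictor is tested on its own and kept as a candidate if p < 0.20. The Power analysis section bases the primary comparison on 80 AIS and 80 ICH patients.

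**The concern.** A marker meant to support the IVT decision has to be read at its concentration before IVT. A draw on arrival gives that concentration. A draw after emergency treatment may not, and the departure is not the same in the two groups. Some AIS patients will have been treated, while ICH patients should not have been, because ICH has to be excluded by imaging first. Exposure to treatment is then tied to the diagnosis being compared.

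Any marker that IVT moves would separate the groups for a reason of no use before treatment. D-dimer and plasminogen are plausible examples because they belong to the fibrinolytic system on which thrombolysis acts, but the article states no effect of IVT on either. The proteomic and metabolomic screen would be open to the same effect. Covariate adjustment offers limited help, since there would be no treated ICH patients from whom to separate treatment from disease.

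**Working it through.** **1. The passages side by side.** Completion of all necessary emergency treatment and arrival at the scene are different moments whenever any treatment is given. The article does not say which governs. The sampling section is the operative instruction for filling the tubes; the Tertiary analysis section states what the analysis assumes. The conflict needs no inference. That the treatment includes IVT is an inference, though a reasonable one on a vehicle that delivers it.

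**2. The plan's own figure.** Inputs from Power analysis: N = 160 (80 + 80), alpha 0.20, power 80%, chi-squared test (taken with 1 df). With non-centrality N·w², 80% power needs w = 0.168, and power at the stated w = 0.17 is 0.81, so the stated w is reproduced. On the scale of means, the detectable difference is

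d = (1.282 + 0.842) × √(1/80 + 1/80) = 2.123 × 0.158 ≈ 0.34.

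The article pairs w = 0.17 with d = 0.30. The conversion 2w/√(1 − w²) gives 0.345, so 0.34 is used here. That label is a separate matter.

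**3. Possible size of the confounding.** Two inputs are not in the article and are assumed:

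- q, the share of the AIS group given IVT before the first draw: 0.2 to 0.7.
- s, the shift IVT causes in a marker, in SDs of the untreated marker: 0.5 to 2.

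The marker has no true AIS–ICH difference. The AIS mean moves by q·s. Mixing treated and untreated patients raises the AIS variance to 1 + q(1 − q)s², so the pooled SD is √{[2 + q(1 − q)s²]/2}. With δ = q·s / [SD × √(2/80)], the chance of p < 0.20 (two-sided, normal approximation to the single-predictor test) is

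P = 1 − Φ(1.282 − δ) + Φ(−1.282 − δ).

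Worked case q = 0.3, s = 1: variance 1.21, pooled SD √1.105 = 1.051, spurious d = 0.30/1.051 = 0.29, δ = 0.30/(1.051 × 0.158) = 1.81, P ≈ 70%.

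| q | s = 0.5 | s = 1 | s = 2 |
|---|---|---|---|
| 0.2 | 28% | 48% | 82% |
| 0.3 | 38% | 70% | 97% |
| 0.5 | 61% | 96% | about 100% |
| 0.7 | 82% | about 100% | about 100% |

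The benchmark is 20%, the rate at which any null marker passes. The lowest corner is only modestly above it. At q = 0.5, s = 1 the spurious d is 0.50/1.061 = 0.47, larger than the 0.34 the study can detect.

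**4. Cost of counting only pre-IVT samples.** If q = 0.5, 40 of the 80 AIS samples remain against 80 ICH:

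d = 2.123 × √(1/40 + 1/80) = 2.123 × 0.194 ≈ 0.41, against 0.34 with all samples.

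**The case against.** The strongest reply is that the bias, unlike the contradiction, is conditional. The sampling section does not name IVT. The Tertiary analysis section and the Discussion both point to an early draw. Figure 2 sets out the order of procedures but is not shown, and it may settle which section describes practice. All of this stands, and it is why the bias is put here as something that can arise. It does not make the two written statements agree.

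Several stronger readings are tempting and are not supported:

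- A reader might infer that many or most AIS samples are post-IVT. The article gives no IVT rate, and the Definitions section counts TIA within AIS.
- A reader might infer that the second sample is affected more than the first. Nothing in the article sizes this.
- A reader might infer that the later validation phase would repeat the artefact. The article says only that a new sample will be used, not how it will be drawn.
- A reader might infer that draw and treatment times go unrecorded, or that no adjustment for onset-to-sample time is planned. Both could sit in the eCRF specification or an analysis plan not shown, so their absence from an article is no finding.

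It can also be said that this is a discovery screen with later testing, so no treatment decision rests on it alone. That lowers the stakes. It does not remove a systematic difference between the groups, which further testing corrects only if the new samples are taken before IVT.

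**Conclusion.** The contradiction between the Blood sampling and processing section and the Tertiary analysis section is certain and needs to be resolved. The confounding of the primary AIS–ICH comparison is a conditional risk. It requires that the sampling section governs, that emergency treatment there includes IVT, and that IVT moves the marker in question. Where these hold, a marker with no diagnostic value passes the screen more often than the nominal 20%: about 28% at q = 0.2 and s = 0.5 SD, 70% at q = 0.3 and s = 1 SD, and 96% at q = 0.5 and s = 1 SD. The true size cannot be derived from the article because neither the IVT share nor the shift is given. Even a modest bias matters for the stated purpose, since a concentration measured after IVT cannot inform whether to give it.

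**What to change.** Reconcile the two sections so that the timing of the first study sample relative to IVT is stated once and fits the pre-treatment purpose, without changing or delaying care. How this fits into the order of emergency procedures is for the clinical team.

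Classify every sample as pre- or post-IVT, report the AIS–ICH results separately by that status, and state that no marker qualifies as a candidate on post-IVT samples alone.

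The cost is a wording change, one classification per sample and one split of the results. The statistical price depends on how many AIS samples prove to be post-IVT: at q = 0.5 the detectable d for the qualifying comparison rises from about 0.34 to about 0.41. AIS patients not given IVT may also be a selected subset, for example with more TIA. If the pre-IVT samples come mainly from such patients, that must be stated as a limitation.

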**Figure 3 F3:**
[figure not shown]
Handling of blood samples. The process of handling blood samples is described here. Details of the exact procedure can be found in the text “collection and processing of blood samples.”

One EDTA tube (6 ml), the heparin tube (5 ml), and the serum tube (5 ml) will be centrifuged with 2,500 × g in a centrifuge (CompactStar CS4, maximum rotation speed 6500 min.^−1^/4000 × g; maximum capacity for 6 tubes; from Avantor™ delivered by vwr™, United States, Radnor, PA) aboard the MSU. After centrifugation, blood cells will be separated from blood plasma. The blood cells and blood plasma originating from the EDTA tube will be divided into 2 × 6 different samples (0.25 ml volume for each sample; six samples for blood cells and six samples for blood plasma) by pipetting them into small “FluidX-tubes.” The blood plasma originating from the heparin and serum tubes will be divided into 8 different samples each (0.25 ml volume for each sample) by pipetting them into different “FluidX-tubes.” The non-centrifugated EDTA tube (3 ml) will be divided into 8 samples of 0.25 ml each and pipetted into “FluidX-tubes.”

The Tempus™ tube (3 ml) will be shaken, non-centrifugated, incubated for 2 h at room temperature, and then stored in a freezer (at −20°C). One drop of full blood is placed on a dry blood card (Whatmann collection cards).

The 36 “FluidX-tubes” can be stored for up to 2 h in a refrigerator (at 4°C) aboard the MSU. The 37 tubes (36 “FluidX tubes” and one Tempus™ tube) and blood card will be transported with the MSU to the fire or rescue station and then stored in a locked freezer (at −20°C) in a secured room. These samples will be transported once a month or in shorter intervals, if necessary, to the fully certified biobank of the Max-Delbrück-Centrum (MDC) and stored there at −80°C. For details on processing, see Figure 3.

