### Statistical analysis

For the primary target, out of all available proteomics and metabolomics data, possible predictors for the differentiation between AIS and ICH are extracted by means of logistic regression. Similar to the selection process for the secondary target, predictors will be chosen to differentiate between AIS (and ICH) on the one side and SM on the other side.

For both targets of this “discovery phase,” all predictors will be tested individually to assess their prediction quality (Hosmer). Predictors with a “significant contribution” (that is, a *p*-value in the Chi-squared test with *p* < α = 0.20) will be acknowledged as suitable candidates and further investigated in the combined Phases 2 and 3 (“Derivation Phase” and “Validation Cohort”) taking place at a later phase of the biomarker project with a new sample.

Additionally, sensitivity, specificity, and predictive values will be tested for potential biomarkers.

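### Time at −20°C varies between patients up to about a month, and the marker screen as stated does not account for it

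*Protocol article*

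**What the plan says.** The protocol article, under Blood sampling and processing (text below Figure 3), describes three storage stages for the 36 FluidX aliquots of each draw:

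- **On board:** they "can be stored for up to 2 h in a refrigerator (at 4°C) aboard the MSU".
- **At the fire or rescue station:** they are "stored in a locked freezer (at −20°C) in a secured room".
- **At the biobank:** "These samples will be transported once a month or in shorter intervals, if necessary, to the fully certified biobank", "and stored there at −80°C".

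The section on primary and secondary targets says that "the absolute values of blood biomarkers and their kinetics in AIS and ICH patients will be determined". The statistical analysis section says that "possible predictors for the differentiation between AIS and ICH are extracted by means of logistic regression" and that "all predictors will be tested individually to assess their prediction quality", with p < 0.20 as the threshold for going forward. Sensitivity, specificity and predictive values are then examined. No covariate is named.

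**The concern.** The refrigerator step is capped at 2 h, but the −20°C step has no limit shorter than the monthly transport. A sample drawn soon after a transfer waits close to a month, and one drawn shortly before a transfer waits far less. The difference comes from the calendar, not from the patient.

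The screen covers untargeted proteomic and metabolomic features whose stability at −20°C cannot be taken for granted across the board. For a feature that degrades, the measured value is the level at draw less a loss that differs between patients. Two things are then at stake:

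1. **Missed candidates.** The extra variance shrinks the standardised difference, and a marker that misses the threshold is not carried to the next phase.
2. **Shifted levels.** Absolute concentrations are on average lower than in fresh blood, whereas the Outcomes section looks ahead to point-of-care use. The stated analysis would not show which candidates are affected.

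**Working it through.** **Inputs from the protocol article.** 80 AIS vs 80 ICH for the primary target; 40 AIS vs 40 stroke mimics for the secondary; alpha 0.20; power 80%; detectable effects w ≥ 0.17 and w ≥ 0.24 (Power analysis section). Default transfer once a month (Blood sampling and processing).

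**Step 1: reproduce the stated power.** Chi-squared test, 1 df, noncentrality N·w².
- Primary: 160 × 0.17² = 4.624, power 80.8%.
- Secondary: 80 × 0.24² = 4.608, power 80.7%.

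Both agree with the stated 80%. With equal groups, d = 2w/√(1 − w²) gives d = 0.345 and 0.494. The article prints 0.30 and 0.40 beside these w values; that is a separate matter, and the w values are used here.

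**Step 2: storage model (assumed).** The document gives no stability data. Assume that time at −20°C is uniform on 0–30 days and unrelated to diagnosis, with linear loss reaching L between-patient SD at day 30. The added variance is L²/12, so d is multiplied by 1/√(1 + L²/12).

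| L (SD lost in 30 days) | Multiplier for d | Power, 80 vs 80 | Power, 40 vs 40 |
|---|---|---|---|
| 0 | 1.000 | 80.8% | 80.7% |
| 0.5 | 0.990 | 80.2% | 80.1% |
| 1 | 0.961 | 78.5% | 78.4% |
| 2 | 0.866 | 72.2% | 72.4% |

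A normal approximation started at d = 0.336 (power 80.1%, 80 vs 80) gives 79.5%, 77.7% and 71.3%, hence about 80%, 78% and 71–72%. At L = 2 the loss equals giving up 1 − 1/(1 + 4/12) = 25% of the sample.

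**Step 3: false differences.** With L = 1 and no true group difference, the simulated rejection rate was 0.202 against the nominal 0.20. Storage time unrelated to diagnosis does not create spurious candidates.

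**Step 4: accuracy with a cut-off found in the study.** Take a marker 2 SD higher in ICH. Without loss, the midpoint cut-off of 1 SD gives 84.1% sensitivity and specificity. With loss, both group means fall by L/2 and the midpoint moves to 1 − L/2. Averaging over the uniform loss, sensitivity and specificity are both 83.9%, 83.1% and 80.5% for L = 0.5, 1 and 2.

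**Step 5: carry-over to fresh blood.** Apply the Step 4 cut-offs (0.75, 0.5 and 0 SD) to fresh samples. Specificity is Φ(0.75) = 77%, Φ(0.5) = 69% and Φ(0) = 50%. Sensitivity is Φ(1.25) = 89%, Φ(1.5) = 93% and Φ(2) = 98%. This shows why a cut-off may not transfer. It does not describe an analysis that the article plans.

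**The case against.** The case against has real force:

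- **No loss is shown.** The article has no stability data for any marker. Without an assumption, all that is established is that storage time varies. This stands, and it is why the size is given only as a range.
- **The power effect is small.** It is under 1 point at 0.5 SD and about 2 points at 1 SD. Only 2 SD costs about 9 points, and nothing in the document makes that loss likely. This stands.
- **A reader might infer that the planned sensitivity and specificity would collapse.** That would need a cut-off fixed in fresh blood and applied to the stored samples. The article fixes no such cut-off, and one found within the study adapts to the mean loss (Step 4).
- **A reader might infer spurious AIS/ICH differences.** Nothing ties time at −20°C to diagnosis, and Step 3 shows the null rate unchanged.
- **Working cut-offs belong to later phases.** This study only selects candidates, which are then tested in a new sample. This limits the carry-over problem but does not remove it: the flag is most useful before candidates move on.
- **A covariate may sit in the full protocol or analysis plan.** That is possible, since testing one marker at a time does not rule out adjustment. The storage rule itself is stated in the article and does not depend on those documents.
- **Kinetics are probably little affected.** Two samples from one patient, 20–60 minutes apart, would normally share freezer and transfer, so a linear additive loss cancels in the difference.

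**Conclusion.** The point holds in a limited form. The article sets a storage time at −20°C that varies between patients up to about a month, and the screen as stated does not account for it. For unstable analytes the consequence is attenuation and a shift in absolute levels. For stable markers there is none.

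The cost in power is negligible to about 2 points for a loss of up to 1 SD over 30 days and about 9 points at 2 SD. In-study sensitivity and specificity fall by at most about 4 points over that range. All of this rests on an assumed uniform 0–30 day stay, linear loss, independence from diagnosis and loss rates that the document does not supply. The document states neither a minimum stay nor the time at −80°C before assay, so it does not support calling the −20°C step the most variable stage.

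This is an inexpensive improvement to a discovery screen, not an error that undermines it.

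**What to change.** 1. **Statistical analysis.** For each sample, derive days at −20°C from the draw date and the transfer date. Regress each marker on it. Include it as a covariate in each marker's logistic model for both targets, or report that model as a sensitivity analysis. Flag any marker whose level depends on storage time before it enters the derivation phase.
2. **Blood sampling and processing.** If samples are still being collected, replace the open-ended monthly default with a stated shorter maximum stay at −20°C. The text already permits shorter intervals. No particular interval follows from the document.

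A separate accuracy estimate in the shortest-stay samples is not worth adding: under the uniform model a 7-day limit leaves about 80 × 7/30 ≈ 19 patients per group.

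**Cost:** one degree of freedom per marker model, two logged dates per sample and, if the interval is shortened, more transport runs. No extra patients or assays are needed, and the first change still works if collection is complete.
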